# Definition of terms/acronyms

| *CONSORT* | *Consolidated standards of reporting trials* |
| --- | --- |
| *MMI* | *Multimedia information resources* |
| *PIS* | *Participant information sheet* |
| *RCT* | *Randomised controlled trial* |
| *SAP* | *Statistical analysis plan* |
| *SWAT* | *Study within a trial* |

# Design

## 2.1 TRECA

The TRECA study is divided into two phases: Phase 1 (development); and Phase 2 (evaluation).

This SAP relates to Phase 2. In this evaluation phase, the MMI will be tested in a series of embedded trials hosted within healthcare trials (SWATs). The MMI will be tailored slightly for each host trial by adding a small amount of content to the MMI specific to that host trial. The MMI will be tested for impact on cognitions (i.e. decisions about trial participation taken by children and adolescents and/or parent/carer) and behaviours (rates of recruitment to, and retention in, the host trials).

This evaluation phase will use an embedded randomised controlled trial (RCT) design, with potential participants in the host healthcare trials receiving one of three versions of the recruitment information: the standard, written trial participant information sheet (PIS) alone; the standard PIS in addition to the MMI; or the MMI only. These will form the three arms of the study. The recruitment, retention and decision making data will be returned to the TRECA team from each of the six host trials, where the data from each trial will be individually analysed and then ultimately combined in meta-analyses by a statistician at the University of York.

Full details of the background and design of the TRECA study are presented in the protocol (version 2.15). Any changes between the protocol and the analysis plan are detailed.

## 2.2 Host Trials

Host trials may use individual or cluster randomisation as deemed practical and appropriate. Although the trials contains three arms, the two arms of PIS only and MMI only are the main area of scientific interest. We added the third (combined) arm as an option in case host trials or the relevant REC was concerned about ‘MMI only’ being used in recruitment.

Further information is given about each of the individual trials below, and a summary of the characteristics of each trial are given in Table 1 and Table 2. As this study looks at all those approached to enter each trial, the number of participants included in TRECA is expected to be higher than the expected sample size, as seen in Table 1.

**BALANCE**: A trial recruiting children with “Lazy eye" (amblyopia) from 3 sites (2 clinics at Moorfields Eye Hospital in London and 1 clinic in Bedfordshire). In this pilot trial, children will receive, at random, either a Nintendo 3DSXL console with movies, or standard patching/blurring eye-drop treatment.

**BAMP**: A single-centre clinical trial assessing the effectiveness of manipulate surgical treatment to bring the upper jaw forwards in 11-14 years old children. BAMP also contains a hypothetical sub study, where participants will be given information about the trial and they will then be asked if they would hypothetically enter the trial. Due to the fact that this is a hypothetical study and hence different in nature to the other host trials, the results from the sub-study will not be included in the meta-analysis. TRECA materials will be used in both recruitment to the main study and the additional hypothetical sub- study.

**CHAMP UK**: A multicentre trial placebo controlled randomised trial which investigates low-dose atropine eye drops to reduce progression of myopia in children.

**FORCE**: A multi-centre prospective randomised trial of a soft bandage and immediate discharge versus current treatment with rigid immobilisation for acute torus fractures of the distal radius in children. For the FORCE trial, cluster randomisation (by recruitment site) is used for the TRECA allocations. We will use only two arms of TRECA (PIS only versus MMI only) to enable the power to be increased and the impact of the MMIs to be more robustly evaluated.

**THERMIC-3**: A multi-centre trial which considers intermittent antegrade warm blood versus cold blood cardioplegia in children undergoing open heart surgery.

**UKALL**: The UKALL trial is a multicentre, phase III, randomised controlled trial, with two phases of randomisations. The aims are to define whether further refinement of minimal residual disease (MRD) based risk stratification and treatment regimen improves survival whilst reducing overall burden of therapy in children and young adults suffering from acute lymphoblastic leukaemia or lymphoblastic lymphoma.

Table 1 is given below outlining the main characteristics of all the host trials. Table 2 gives the details of the hypothetical study in BAMP. The type of questionnaire are as follows:

- Y = younger patient version
- O = older patient version
- P/F = patient family version

Table 1 – Host trial summary

| Trial | Target Sample Size | Expected TRECA sample size | Type of randomisation in trial | Type of randomisation in TRECA | TRECA arms being used | Decision making questionnaires used |
| --- | --- | --- | --- | --- | --- | --- |
| BALANCE | 66 | 100 | Individual | Individual | PIS, MMI or both | Y, P/F |
| BAMP | 60 | 10 | Individual | Individual | PIS, MMI or both | O, P/F |
| CHAMP-UK | 289 | 413 | Individual | Individual | PIS, MMI or both | Y, P/F |
| FORCE | 696 | 1071 | Individual | Cluster | PIS or MMI | P/F |
| THERMIC-3 | 94 | 118 | Individual | Individual | PIS, MMI or both | Y, O, P/F |
| UKALL | 40 | 50 | Individual | Individual | PIS, MMI or both | Y, O, P/F |

Table 2 – Characteristics of hypothetical BAMP sub-study

| Trial | Target Sample Size | Expected TRECA sample size | Type of randomisation in TRECA | TRECA arms being used | Decision making questionnaires used |
| --- | --- | --- | --- | --- | --- |
| BAMP sub-study | 148 | 148 | Individual | PIS or MMI | O |

# Trial Objectives

The immediate aims of TRECA are to evaluate the potential for MMIs to improve the quality of decision making about participation in healthcare trials involving children and adolescents, and to assess the impact on trial recruitment and retention.

The long-term aim of the project is to increase the available clinical evidence base for the treatment of children and adolescents, including those with long-term health conditions.

The aim of this phase of TRECA is to evaluate the MMI in a series of SWATs, and test their effects on recruitment and retention rates, and decision-making, by comparing the effects of providing standard written participant information with provision of the MMIs either in addition to the standard written participant information or the provision of the MMIs alone.

Hence, the two pairwise comparisons of the three TRECA arms of interest are whether the MMI provision could replace (MMI only vs PIS only) or supplement (MMI & PIS vs PIS only) the standard written participant information. The results of the individual trials will be combined statistically in a meta-analysis, as described in Section 8.

# Sample Size

## 4.1 Overall

The sample size for each SWAT will ultimately be determined, and constrained, by the number of people approached to take part in the host trial.

An example sample size calculation based on the expected baseline recruitment rate of the host trials (that is, their recruitment rate without the intervention), is provided. A baseline recruitment rate of 20% to 80% is assumed, to account for the known variation in trial recruitment rates. Given this uncertainty, we estimated the sample size based on the relative effect of the MMI alone (when compared to PIS alone). Further, we assumed 80% power at standard 5% Type I error (α rate) to detect the specified effect and we have characterised the effect size as an odds ratio, which is more robust for sample size calculation.

Assuming the typical recruitment rate is 20%, an odds ratio of 1.2 would mean an increase in recruitment rate using the MMI to 23.1%. To detect this in a single randomised controlled trial (with 1:1 randomisation between MMI and printed material arms), a sample size of 701 would be needed. If the typical recruitment rate is 80%, an odds ratio of 1.2 corresponds to an increase in recruitment rate to 82.8% and would require a sample size of 783.

Results from each embedded trial will ultimately be combined in a meta-analysis. Given that there will be different trials with variation in interventions, participants and baseline recruitment rates, it is plausible that the effectiveness of the MMIs at improving recruitment will vary; i.e. there will be heterogeneity in the observed odds ratios across trials. Adjusting for this is approximate (particularly as the heterogeneity is currently unknown), however, as a rough rule of thumb if the I2 statistic in the meta-analysis is 50% the sample size will double (1).

Given the three arm randomisation (with two of the arms being compared for the primary analysis), an additional 50% of people will need to be approached (i.e. 783 x 1.5 = 1,175). Furthermore, the adjustment for heterogeneity in effects of the MMI intervention across the six trials (estimated I-square value = 50%) means that the sample size should be doubled (i.e. 1,175 x 2 = 2,350).

Therefore, the six embedded trials in TRECA should (on average) each be approaching 392 people, assuming a baseline trial recruitment rate between 20% and 80% of those approached. We will make pragmatic decisions about inclusion of each host trial into TRECA, in part to attain variation among the included trials in aspects of the intervention and setting, and in part to ensure that we recruit a full complement of embedded trials to TRECA. Further, trials involving children and adolescents are often relatively small: our random sample survey of 100 trials involving children and adolescents with long-term conditions (2) found that only two-thirds had a target sample size of >216. Given the other entry criteria applied to host trials, one or more of the host trials recruited to TRECA may have a smaller target sample size than 216. Consequently the meta-analysis of the 6 embedded trials may be required to provide a robust evaluation of the MMIs’ effectiveness.

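### The sample sizes of 701 and 783 for an odds ratio of 1.2 are about one-eighth of what 80% power requires, and 1,175, 2,350 and 392 inherit the error

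*SAP*

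**What the plan says.** SAP section 4.1 sets the terms: "we assumed 80% power at standard 5% Type I error (α rate) to detect the specified effect", with the effect expressed as an odds ratio of 1.2. It works two cases for a single trial randomised 1:1 between MMI and printed material.

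- At the low end: "Assuming the typical recruitment rate is 20%, an odds ratio of 1.2 would mean an increase in recruitment rate using the MMI to 23.1"%, for which "a sample size of 701 would be needed".
- At the high end: "If the typical recruitment rate is 80%, an odds ratio of 1.2 corresponds to an increase in recruitment rate to 82.8"%, which "would require a sample size of 783".

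The larger figure is then multiplied by 1.5 for the third arm, giving 1,175. Next, for an assumed I-squared of 50%, "the sample size should be doubled (i.e. 1,175 x 2 = 2,350". Dividing by six leads to the conclusion that "the six embedded trials in TRECA should (on average) each be approaching 392 people".

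This is the only power statement in the SAP for the primary outcome. Section 4.2 concerns a different outcome in the hypothetical BAMP sub-study.

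**The concern.** A rise of about three percentage points in recruitment is a small difference between two proportions, and such differences usually need several thousand people. Totals in the hundreds are implausible on their face.

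At stake is the relation the SAP asserts between sample size, power and effect for its primary comparison. If the base figure is wrong, the overall and per-trial targets built on it are wrong too, and a reader has no sound statement of what the pooled analysis can detect.

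**Working it through.** **Inputs.** All but the first come from section 4.1.

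- Two-sided testing is my assumption, because the SAP does not state sidedness.
- α = 0.05 and power = 0.80, so z = 1.960 and 0.8416.
- Odds ratio 1.2, 1:1 allocation, baselines of 20% and 80%.

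**Step 1: the rates.** Odds of 0.25 × 1.2 = 0.30 give 0.30/1.30 = 23.08%. Odds of 4 × 1.2 = 4.8 give 4.8/5.8 = 82.76%. Both agree with the SAP.

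**Step 2: number per arm.** With p̄ the mean of p₁ and p₂,

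n = [1.960·√(2p̄(1−p̄)) + 0.8416·√(p₁(1−p₁) + p₂(1−p₂))]² / (p₂−p₁)².

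- 20% v 23.08%: (1.960 × 0.5814 + 0.8416 × 0.5810)² / 0.03077² = 2.652 / 0.0009467 ≈ 2,801 per arm, 5,602 in total.
- 80% v 82.76%: (1.960 × 0.5505 + 0.8416 × 0.5502)² / 0.02759² = 2.378 / 0.0007610 ≈ 3,125 per arm, 6,250 in total.

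The ratios to the stated figures are 5,602/701 = 7.99 and 6,250/783 = 7.98.

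**Step 3: can the stated figures be reproduced?** No standard variant gives 701 or 783 (totals at 20% and 80%):

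| Variant | 20% | 80% |
|---|---|---|
| One-sided 5% | 4,414 | 4,924 |
| Continuity correction, two-sided | 5,732 | 6,394 |
| Rounded rates (23.1%, 82.8%), two-sided | 5,522 | 6,062 |

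The log-odds-ratio formula, 7.849 × [1/(p₁(1−p₁)) + 1/(p₂(1−p₂))] / (ln 1.2)², gives 2,805.9 and 3,130.5 per arm. A quarter of each is 701.5 and 782.6, very close to the stated figures.

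**Step 4: power at the stated numbers.** Power = Φ{[(p₂−p₁)√n − 1.960·√(2p̄(1−p̄))] / √(p₁(1−p₁) + p₂(1−p₂))}.

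- As two-arm totals: n = 350.5 gives Φ(−0.970) = 16.6%, and n = 391.5 gives Φ(−0.969) = 16.6%.
- As numbers per arm: 28.8% in both cases. The ×1.5 step excludes this reading, because adding a third equal arm multiplies a two-arm total by 1.5.
- Odds ratio detectable with 80% power at those totals: about 1.64 (20%) and 1.73 (80%).

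**Step 5: the chain.** The SAP's multiplications are sound within rounding: 783 × 1.5 = 1,174.5; 783 × 1.5 × 2 = 2,349; 2,349/6 = 391.5. Only the base is wrong. The SAP's own factors applied to 6,250 give 9,375, then 18,750, then 3,125 per trial.

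The factor of 1.5 does not fit the design, however. FORCE uses two arms and supplies 1,071 of the 1,762 people expected in Table 1 (100 + 10 + 413 + 1,071 + 118 + 50). People in MMI only or PIS only number 1,071 + ⅔ × 691 ≈ 1,532, so the arm factor is 1,762/1,532 = 1.15. That gives roughly 6,250 × 1.15 ≈ 7,190; × 2 ≈ 14,380; / 6 ≈ 2,400 per trial, before any design effect for clustering.

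**Step 6: what Table 1 supports.** Treat the 1,532 as one 1:1 comparison (766 per arm) with a common baseline. The doubling for I-squared 50% halves the effective number to 383 per arm.

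| Baseline | Power for OR 1.2, no heterogeneity | Power for OR 1.2 with the doubling | OR detectable at 80% power with the doubling |
|---|---|---|---|
| 20% | 31% | 18% | 1.61 |
| 50% | 43% | 24% | 1.50 |
| 80% | 28% | 16% | 1.74 |

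None of these allows for cluster randomisation in FORCE.

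**The case against.** The strongest reply is that section 4.1 calls this an example, says that the number approached in each host trial fixes and limits the sample, treats the heterogeneity adjustment as approximate, and looks to the meta-analysis for a robust answer. Table 1 already falls short of the SAP's own 2,350, so the figures do not drive recruitment, and no model or estimand depends on them. That is fair, and it is why nothing beyond the text of section 4.1 has to change. It does not make the stated relation true: the section still says that these numbers give 80% power for an odds ratio of 1.2, and it draws a per-trial target from them.

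Three stronger readings are tempting, and the document does not support them.

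- A reader might take 9,375, 18,750 and 3,125 as the correct replacements. They only carry forward a three-arm factor that does not fit FORCE.
- A reader might infer that a non-significant pooled result will be reported as no effect. The SAP does not say so; sections 7.2 and 8 report odds ratios and forest plots with confidence intervals.
- The near match to a quarter of the per-arm number suggests how the slip arose, but the SAP shows no formula, so the cause remains a guess.

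**Conclusion.** The point stands as an arithmetic error that is wrong as written. The discrepancy is a factor of about eight in the totals. It survives a change of formula, a continuity correction and rounding of the rates; one-sided testing still leaves a factor of about 6.3 (4,414/701 and 4,924/783). By the SAP's own logic the power at 2,350 is also about 17%, since its two inflation factors only offset the third arm and the heterogeneity.

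The base totals of 5,602 and 6,250 rest only on section 4.1's inputs and two-sided testing. The figures at Table 1 numbers are less firm. They assume the expected sizes are met, equal allocation in the three-arm trials, a common baseline rate, and the SAP's rule that I-squared of 50% doubles the requirement. Clustering in FORCE would be expected to lower the power further.

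**What to change.** In section 4.1:

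1. Replace 701 and 783 with about 5,602 and 6,250, say that these are two-arm totals, and state that the test is two-sided.
2. Recompute the later figures with an arm factor that reflects two-arm FORCE (about 1.15 on the Table 1 mix), and say whether a design effect for FORCE is included.
3. Withdraw the statement that the study has 80% power for an odds ratio of 1.2.
4. State instead the power for that odds ratio, and the odds ratio detectable with 80% power, at the Table 1 numbers across baselines of 20–80%, with and without the doubling.

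This changes SAP wording only. It calls for no further recruitment and alters no analysis.

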# Randomisation

Allocation to groups will be achieved by random number generator or another randomisation method that suits the practicalities of the host trial. Participants will be randomised 1:1 to either PIS or MMI (two arms) in the BAMP sub-study. In FORCE clusters (hospitals) are randomised to either PIS or MMI. Otherwise, participants will be randomised 1:1:1 to one of PIS, MMI or both.

Masking of the allocation at outcome measurement is not possible but also irrelevant: the patient cannot be masked to the information format s/he will receive but, as s/he will be unaware of the embedded information trial, a lack of masking will not affect his/her responses on the self-completion measures, or have any biasing effect on their decisions on trial participation or continuation.

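### The 1.5 multiplier for a third arm is applied to all six hosts, although FORCE (61% of expected people) has two arms; at the Table 1 mix it is about 1.15 before any allowance for FORCE's clustering

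*SAP*

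**What the plan says.** Section 4.1 of the SAP builds the overall requirement in three steps.

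- **Base.** For a two-arm 1:1 comparison, "we assumed 80% power at standard 5% Type I error (α rate) to detect the specified effect". At a 20% baseline recruitment rate, "a sample size of 701 would be needed". At an 80% baseline, "an odds ratio of 1.2 corresponds to an increase in recruitment rate to 82.8% and would require a sample size of 783".
- **Third arm.** "Given the three arm randomisation (with two of the arms being compared for the primary analysis), an additional 50% of people" are added to the number approached, so 783 becomes 1,175.
- **Heterogeneity.** An assumed I-squared of 50% doubles this to 2,350. Spread over the six embedded trials, they "should (on average) each be approaching 392 people".

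The design sections describe FORCE differently from the other hosts. Section 2.2 says that FORCE uses two arms, with the aim of gaining power, and that TRECA allocation there is by recruitment site. The Randomisation section repeats it: "In FORCE clusters (hospitals) are randomised to either PIS or MMI". The Table 1 row reads "FORCE | 696 | 1071 | Individual | Cluster | PIS or MMI | P/F", where 1071 is the expected TRECA sample. Sections 7.3.1 and 8.1 accordingly leave FORCE out of the combined-arm comparison.

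**The concern.** A factor of 1.5 is right when every host places a third of its people in an arm that the primary comparison does not use. FORCE places nobody there, and it is by far the largest host. Section 4.1 was therefore not reconciled with the design in section 2.2 and Table 1.

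The same two-arm arrangement is allocated by hospital, which costs information that section 4.1 does not count. So one feature of FORCE makes 1.5 too large and another is missing altogether.

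What is at stake is how the stated requirement is read against expected numbers. Setting the 1,762 people of Table 1 against 2,350 compares a mixed two-arm and three-arm, partly clustered programme with a figure for six individually randomised three-arm trials. If the base is later corrected and 1.5 is left in place, the mismatch carries into the new total.

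**Working it through.** **1. The plan's own chain.** 783 × 1.5 = 1,174.5, rounded to 1,175; 1,175 × 2 = 2,350; 2,350 / 6 = 391.7, rounded to 392. The multiplication is correct.

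**2. Expected people, from Table 1.**

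- Three-arm hosts: BALANCE 100 + BAMP 10 + CHAMP-UK 413 + THERMIC-3 118 + UKALL 50 = 691.
- Two-arm host: FORCE 1,071.
- Total: 691 + 1,071 = 1,762. FORCE share: 1,071 / 1,762 = 60.8%.

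**3. Third-arm multiplier at this mix.** With 1:1:1 allocation, two thirds of the three-arm hosts fall in MMI only or PIS only: 691 × 2/3 = 460.7. All of FORCE does.

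- People in the two compared arms: 460.7 + 1,071 = 1,531.7.
- Multiplier: 1,762 / 1,531.7 = 1.150.
- Against the plan: 1.5 / 1.150 = 1.30. This ratio does not depend on the base or on the doubling.

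The result depends on the mix. With six equal hosts, one of them two-arm, the multiplier would be 1 / (1/6 + 5/6 × 2/3) = 1.385, and 1.5 / 1.385 = 1.08.

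**4. FORCE's clustering.** The SAP gives no intracluster correlation (ICC) or cluster size, so the design effect (DE) below is an assumed range. Multiplier = 1,762 / (1,071/DE + 460.7).

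| Assumed DE for FORCE | Effective number in compared arms | Overall multiplier |
| --- | --- | --- |
| 1.0 | 1,071.0 + 460.7 = 1,531.7 | 1.15 |
| 1.2 | 892.5 + 460.7 = 1,353.2 | 1.30 |
| 1.5 | 714.0 + 460.7 = 1,174.7 | 1.50 |
| 2.0 | 535.5 + 460.7 = 996.2 | 1.77 |

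With DE = 1 + (m − 1) × ICC, a DE of 1.5 needs an ICC of 0.5/19 = 0.026 at m = 20 per site, or 0.5/49 = 0.010 at m = 50.

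**5. The base to which the multiplier is applied.** Inputs from section 4.1: odds ratio 1.2, 80% power, 5% alpha (two-sided assumed, since sidedness is not stated), 1:1 allocation. Per-arm size, with p̄ the mean of p1 and p2:

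n = [1.96 × √(2p̄(1 − p̄)) + 0.842 × √(p1(1 − p1) + p2(1 − p2))]² / (p2 − p1)²

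- Baseline 20%: odds 0.25 × 1.2 = 0.30, so p2 = 0.30/1.30 = 23.1%. n = 2,801 per arm, 5,602 in total. Stated: 701. Ratio 5,602/701 = 8.0.
- Baseline 80%: odds 4 × 1.2 = 4.8, so p2 = 4.8/5.8 = 82.8%. n = 3,125 per arm, 6,250 in total. Stated: 783. Ratio 6,250/783 = 8.0.

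One-sided tests, rounded rates, a continuity correction, the log-odds-ratio formula and the arcsine formula do not recover 701 or 783 either. The smallest totals among these variants are 4,350 and 4,774 (one-sided, rounded rates).

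**6. Combined effect, keeping the plan's doubling.**

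- Multiplier 1.15 (DE 1.0): 5,602 × 2 × 1.150 = 12,889 and 6,250 × 2 × 1.150 = 14,380 (unrounded multiplier).
- Multiplier 1.50 (DE 1.5): 5,602 × 2 × 1.5 = 16,806 and 6,250 × 2 × 1.5 = 18,750.

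**The case against.** The strongest defence is that section 4.1 offers an example calculation, says that size is constrained by the host trials, and gives 392 only as an average. No section says that recruitment is judged against 2,350 or 392. That stands, and it limits the consequence. It does not make the factor fit the design: the SAP attributes 1.5 solely to the third arm, and FORCE has none.

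A second defence is that 1.5 may be about right once clustering is counted, since an assumed design effect of 1.5 for FORCE gives exactly 1.50. The arithmetic stands, but the SAP does not argue this and states no design effect. Agreement at one assumed value is not a justification. It does show that neither the size nor the direction of the net error is settled by the documents.

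Third, the pooled analysis is a random-effects meta-analysis, which does not weight FORCE's people one for one. That is fair; the multiplier here is a head count, as the plan's own is.

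A reader might go further and infer that 2,350 and 392 are overstated by 30%, and that the requirement is really 783 × 2 × 1.150 = 1,801, or 300 per trial. The documents do not support this. It takes 783 as given, although 783 does not follow from the stated inputs, and it sets the FORCE design effect to 1. Nor should the 1,532 people expected in the compared arms be set against 783 × 2 = 1,566 and reported as a 2% gap. With 766 per arm, power for an odds ratio of 1.2 is about 31% at a 20% baseline and 28% at 80%, before heterogeneity or clustering.

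**Conclusion.** The point holds as a wrong stated factor. Section 4.1 applies 1.5 to all six hosts, while the third-arm multiplier at the SAP's own expected mix is about 1.15 before clustering. So 2,350 and 392 do not describe the adopted design.

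The 1.15 rests on the Table 1 numbers and on 1:1:1 allocation in the five other hosts. With a design effect for FORCE between 1.0 and 2.0, which is an assumption, the overall multiplier lies between 1.15 and 1.77.

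No downward revision follows. On the stated odds ratio, power and alpha, even the 1.15 multiplier gives about 12,900 to 14,400 people, so 2,350 is too small by a factor of about 5.5 to 6.1 (12,889/2,350 to 14,380/2,350). The multiplier is one component of a calculation that has to be redone as a whole.

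**What to change.** In section 4.1:

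- State the requirement as people in the two compared arms (MMI only and PIS only), not as people approached times a single factor.
- Count the five three-arm hosts at two thirds, and count FORCE's 1,071 divided by a stated design effect. Give the ICC and cluster size behind it, or show a range such as the one above.
- Restate 2,350 and 392 only together with a corrected base for the odds ratio of 1.2, and state whether alpha is two-sided. Do not replace them with 1,801 and 300.

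This is a change of SAP wording; enrolment and allocation need not change. The cost is that the restated requirement will look less favourable against the 1,762 expected people than the present one does.

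### The base sample sizes in SAP Section 4.1 (701 and 783 for an odds ratio of 1.2) are one quarter of the per-arm number needed, and cluster allocation in FORCE is not allowed for, so the stated 80% power does not follow

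*SAP*

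**What the plan says.** Section 4.1 of the SAP assumes a baseline recruitment rate between 20% and 80% and states its error rates: "we assumed 80% power at standard 5% Type I error (α rate) to detect the specified effect". For the 20% baseline (rising to 23.1%) it says: "with 1:1 randomisation between MMI and printed material arms), a sample size of 701 would be needed". For the 80% baseline: "an odds ratio of 1.2 corresponds to an increase in recruitment rate to 82.8% and would require a sample size of 783".

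It multiplies 783 by 1.5 because a third arm is randomised but not part of the primary comparison, then doubles the result for an assumed I-squared of 50% ("i.e. 1,175 x 2 = 2,350"). From this it concludes that "the six embedded trials in TRECA should (on average) each be approaching 392 people".

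Table 1 in Section 2.2 gives the expected TRECA numbers: BALANCE 100, BAMP 10, CHAMP-UK 413, FORCE 1,071, THERMIC-3 118 and UKALL 50. The FORCE row reads "FORCE | 696 | 1071 | Individual | Cluster | PIS or MMI | P/F": two arms, allocated by cluster. Section 5 confirms that hospitals are the unit in FORCE and that the other host trials randomise 1:1:1. Section 7.2 fits the FORCE cluster as a random effect. Section 4.1 gives no intracluster correlation (ICC), site count or design effect.

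**The concern.** An odds ratio of 1.2 moves recruitment by only about three percentage points at either baseline. Detecting that with 80% power takes thousands of people per arm, so a total of 701 or 783 is not credible on its face. The larger figure is the base of everything that follows in Section 4.1, so an error there passes unchanged into 1,175, 2,350 and 392.

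This is the SAP's only sizing of the primary outcome. If it stands, a pooled odds ratio whose interval includes 1 may be read as coming from a programme sized to find a ratio of 1.2, when most such effects would have been missed. Clustering works in the same direction: FORCE dominates the primary comparison, and its people do not carry the information of individually randomised ones.

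**Working it through.** **Inputs.** From Section 4.1: odds ratio 1.2; 80% power; 5% Type I error (sidedness not stated, two-sided assumed, so z = 1.960 and 0.842); baselines 20% and 80%; multipliers 1.5 and 2. From Table 1: the six expected sizes.

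**1. The plan's own chain.** 783 x 1.5 = 1,174.5; x 2 = 2,349, printed as 2,350; 2,350 / 6 = 392. The treated rates also agree with an odds ratio of 1.2: 0.25 x 1.2 = 0.30 odds, or 23.1%; 4 x 1.2 = 4.8 odds, or 82.8%. These steps reproduce.

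**2. The base figures, log odds ratio formula.** n per arm = (1.960 + 0.842)² x [1/(p1q1) + 1/(p2q2)] / (ln 1.2)², where (1.960 + 0.842)² = 7.849 and (ln 1.2)² = 0.03324.
- 20% baseline: 7.849 x (6.250 + 5.633) / 0.03324 = 2,806 per arm. One quarter is 701.5.
- 80% baseline: 7.849 x (6.250 + 7.008) / 0.03324 = 3,131 per arm. One quarter is 782.6.

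The printed 701 and 783 are thus a quarter of the per-arm number at both baselines, or an eighth of the two-arm total. A constant factor suggests a slip in the formula rather than a different method.

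**3. Check by another formula.** The two-proportion formula with pooled variance gives 2,801 and 3,125 per arm (5,602 and 6,250 in total). One-sided, continuity-corrected, arcsine and one-sample variants, and 90% power, do not give 701 or 783 either, whether read as a total or per arm.

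**4. Power from the printed figures** (two-proportion formula, odds ratio 1.2).
- 701 in total at a 20% baseline: about 17%. 783 in total at 80%: about 17%.
- 783 read as per arm (1,566 in total) at 80%: about 29%.
- The full 2,350 over three equal arms puts 2,350 x 2/3 = 1,567 people in the comparison: about 29% at an 80% baseline and 32% at 20%, before any heterogeneity.

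**5. People in the primary comparison.** The trials other than FORCE sum to 100 + 10 + 413 + 118 + 50 = 691, of whom two thirds (461) are in MMI only or PIS only. Adding all 1,071 from FORCE gives 1,532, with FORCE at 1,071 / 1,532 = 70%.

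**6. Power at the Table 1 numbers**, treating the six trials as one two-arm comparison with a common baseline.

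| Baseline | Power, 1,532 compared | Power, information halved (I-squared 50%) | Odds ratio detectable with 80% power | Same, information halved |
| --- | --- | --- | --- | --- |
| 20% | 31% | 18% | 1.41 | 1.61 |
| 50% | 43% | 24% | 1.33 | 1.50 |
| 80% | 28% | 16% | 1.46 | 1.74 |

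**7. FORCE clustering.** Design effect = 1 + (1,071/sites - 1) x ICC. The SAP gives neither input; 15 to 30 sites and ICC 0.01 to 0.05 are assumed.
- 30 sites, ICC 0.01: 1 + 34.7 x 0.01 = 1.347; 1,071 / 1.347 = 795; plus 461 = about 1,256.
- 15 sites, ICC 0.05: 1 + 70.4 x 0.05 = 4.52; 1,071 / 4.52 = 237; plus 461 = about 698.

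Over this range the 1,532 people are worth about 700 to 1,260.

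**The case against.** The calculation is labelled an example, and Section 4.1 says that the size of each embedded trial is set by how many people the host trial approaches. It also warns that some host trials may be small and that the meta-analysis may have to carry the evaluation. Nowhere does the SAP say that the Table 1 numbers deliver 80% power. All of that stands, and it means that no promise about the expected numbers has been broken. It does not make the arithmetic right: the section draws a per-trial requirement from the example, and the SAP offers no other justification.

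A reader might set the Table 1 total of 1,762 against 2,350 and infer that the programme expects only three quarters of its own requirement. The documents do not support that. The factor 1.5 pays for a third arm that FORCE does not have, and Section 2.2 says FORCE was limited to two arms to raise power. On people compared, the plan expects 1,532 against its own 783 x 2 = 1,566, a gap of 2%. If the printed base were right, power before clustering would still be about 79%. Treating 2,350 as the true target would also mislead, because reaching it would not give 80% power.

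A reader might also call the doubling for heterogeneity an error. Section 4.1 presents it as approximate, with heterogeneity unknown, so the power figures above use the plan's own factor. Finally, clustering is handled in the analysis (Section 7.2). The gap is in the sizing only, and its extent rests on assumed inputs.

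**Conclusion.** The concern holds. The figures 701 and 783 are wrong for the assumptions printed beside them, by a factor of four per arm and eight in total, and 1,175, 2,350 and 392 inherit the error. This rests only on two-sided 5% alpha and standard formulas.

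At the Table 1 numbers, power for an odds ratio of 1.2 is about 28-43% over baselines of 20% to 80%, and about 16-24% with the plan's own allowance for I-squared 50%. These ranges assume a common baseline across trials and no clustering. The missing design effect for FORCE lowers them further, by an amount that the SAP does not allow a reader to fix. The Table 1 total of 1,762 is context and not a separate shortfall.

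The planned estimates and confidence intervals are unaffected. What is wrong is the statement of what the programme can detect.

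**What to change.** Amend Section 4.1 of the SAP as follows.

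- Replace 701 and 783 with recomputed figures, stating the formula, whether alpha is two-sided, and whether each number is per arm or in total. Carry the correction through 1,175, 2,350 and 392.
- Apply the third-arm factor only to the host trials that use three arms.
- Add a design effect for FORCE from its actual site count and a stated ICC, with a short sensitivity range.
- Replace the closing requirement of 392 per trial with the power at the Table 1 numbers, or the odds ratio detectable with 80% power. Before clustering, that ratio is about 1.33-1.46 without heterogeneity and about 1.50-1.74 with the plan's doubling for I-squared 50%. It is larger once FORCE clustering is included.

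The cost is a recalculation, revised wording and an entry in the amendment log. The stated power becomes less favourable. Recruitment, the primary comparison and the planned models do not change.
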